### Interactions, covariates and cross-validation

Under each of these aims, we will evaluate if the interaction of the DLPFC-anchored cognitive control network with resting attention and default mode networks, and the sgACC, further moderates these relationships. In each analysis, we will model sex, medication, medication change, comorbidity, substance use, and premorbid function as covariates. We will employ cross-validation techniques, as used in our prior pharmacotherapy and imaging trials [14, 73, 74], to assess the rigor of our inferences.

### Exploratory analyses

We will pursue the following additional exploratory options: 1) covariation due to stimulation site quantified by our gel capsule method, 2) canonical correlations to quantify dimensional relations between connectivity, behavior and symptom, function and suicidality measures, 3) predictive regression models to further interrogate our hypotheses that circuit-behavior measures are response biomarkers of TMS response and predictive markers of functional/suicidality outcomes, 4) machine-learning methods to discover how our data form naturally organized clusters of TMS response trajectories. We will use principal components analysis for data reduction, clustering algorithms (e.g., hidden Markov models) to identify cohesive subgroups defined by circuit dysfunctions, and GLMs to assess if clusters are differentiated by behavior-symptom-functional-suicidality profiles and TMS-related clinical outcomes and, 5) a whole brain voxel-wise approach to quantify circuits and regions within circuits that might be missed by using a priori circuits and regions of interest.

## Data management

### Behavioral and cognitive data management

Data, once acquired, will be coded and given a generic indicator (e.g. 001). Individuals who are listed on the protocol will have access to all coded study data. Coded data will be shared with participating sites for data analysis. All research staff will undergo training from the lead investigator at each site, including the means through which confidentiality is maintained, the proper procedures as dictated by study protocol, and a review of any operating procedures that are important for data collection and veteran safety and security. Standard operating procedures will be shared with participating sites and an overall training log will be kept up to date to ensure collaborating sites are collecting data and running veteran visits in a standardized way. All information regarding prescription of the treatment parameters are monitored throughout the course of treatment and captured in the VA National Clinical TMS Program Quality Improvement Project. VA HIPAA authorization approved by IRB and embedded in the consent form allows for access to this clinical data.

Shared, coded data will be transferred through a secure file transfer software. The sharing of any PHI, if necessary, over the course of the study, will follow the coordinating sites guidance for best practice. The sharing of VA PHI will happen as permitted by VA HIPAA authorization embedded in VA consent.

### MRI data management

MRI acquisitions will be transferred from each facility to the central facility at Stanford through secure transport. All MRI data will be anonymized including removing sensitive subject information and defacing structural images. The data storage system can only be accessed securely by certain investigators using two factor authentication. The storage system is scalable to large datasets and snapshots are recorded over time to prevent any possibility of data loss.

### Data monitoring and safety reporting

A Data Safety and Monitoring Plan will be in place, consistent with standard protocols at the participating sites. Veteran recruitment, protocol compliance, and adverse events (AEs) will be tracked for each site on a semi-annual basis to monitor veteran safety, study progress, and efficacy; and to make recommendations for study continuation. All AEs will be recorded on standard forms and will indicate the severity, date of onset, and likelihood that the AE is related to a study procedure. The PI will ensure that all measures necessary to resolve the SAE are taken and that the Institutional Review Board is notified as soon as is practical in accordance with local institutional policy.

## Discussion

Despite the wide scale adoption of repetitive transcranial magnetic stimulation, we still lack mechanistically-driven biomarkers designed to identify who is most likely to respond, and why. The identification of more precise solutions for MDD patients is imperative given that pharmacoresistant depression can be life threatening. Our study addresses this need through a systematic evaluation of brain circuit biomarkers in patients taking part in the VA Clinical TMS Program. We use a prospective design to evaluate cognitive control network connectivity as a predictive biomarker of the clinical effect of repetitive transcranial magnetic stimulation, and as a response biomarker of change with TMS.

### Strengths

Innovations in our study design include 1) adequate power to interrogate imaging markers, 2) standardization to minimize variability, 3) implementation of a longitudinal design to quantify TMS-related changes in imaging markers, 4) integration of task-evoked and resting state imaging markers, and 5) establishing the foundations for expanding lessons learned to additional diagnoses and parameters.

#### Adequate Power

Our study will be the first pragmatic, large scale mechanistic trial to use functional connectivity neuroimaging and behavioral biomarkers of cognitive control as targets for response and prediction of outcomes in pharmacoresistant patients. Reflective of the emergence of TMS research, previous neuroimaging studies of TMS have employed small samples (mean n= ~ 24) [10]. Our target of 100 patients will ensure statistical power to test our hypotheses.

#### Standardization to minimize variability

Our study will rigorously standardize TMS and neuroimaging protocols and the analytic pipeline (including stringent motion correction). Drawing conclusions about the utility of neuroimaging biomarkers has been difficult from current knowledge given the juxtaposition of small sample sizes and variability in neuroimaging/connectivity analysis, methods, and TMS delivery. By implementing a standardized approach in a well-powered sample, we will be in a unique position to parse variance due to biomarkers of interest versus variance due to other factors.

#### Implementation of longitudinal design

We will be obtaining fMRI scans at three time points during the course of TMS (baseline, after 1 Week and Post-treatment), while other TMS neuroimaging studies have obtained images at only one (Baseline) or two time points (Baseline and Post-treatment). Our approach will allow us, for the first time, to investigate whether change in functional connectivity of particular neural circuits in response to TMS may serve as an early biomarker (i.e., after only a few TMS sessions) of the subsequent effect of TMS. This information could enable clinicians to discontinue an intensive therapy for certain patients early in the TMS course, allowing the right treatment to be identified more quickly, aborting unnecessary side effects, and lowering the risk of patients disengaging from care due to frustration.

#### Task-evoked and resting state imaging markers

The majority of TMS neuroimaging studies have relied heavily on resting state imaging [10]. Our cognitive control measures will allow us to probe our biomarkers of the DLPFC-anchored cognitive control network, elicited during GoNoGo and working memory tasks, and its connectivity with resting circuits involved in regulation. Additionally, if our broad hypothesis is correct that connectivity and behavioral performance changes are correlated, then behavioral measures may be used as proxies for neuroimaging data in clinical practice. Such a finding would offer a scalable TMS response biomarker that complements our mechanistic understanding based on neuroimaging measures of circuit connectivity.

#### Expanding lessons to additional diagnoses and parameters

Given dysfunction in cognitive control and associated circuits are transdiagnostic [75], our findings will be a foundation for expanding to other psychiatric disorders in future trials. Our proposed sample will be sufficiently representative of the comorbidities in pharmacoresistant MDD patients to facilitate a future such transdiagnostic approach.

### Limitations

Our study design also presents certain limitations including 1) the lack of a control group inherent in the observational design, 2) the definition of biomarkers, 3) the co-administration of neuromodulation and psychotropic medications, 4) presence of cognitive control dysfunction in our study population, 5) use of the Beam-F3 method for stimulation targeting vs. neuronavigation methods, 6) choice of stimulation site and parameters, and 7) the overrepresentation of older, male veterans in our population.

#### Lack of control group

Our study is observational and therefore lacks a control group. Veterans receive the standard TMS protocol for MDD as part of their clinical care through the VA’s Clinical TMS Program.

#### Definition of biomarkers

We follow the BEST (Biomarkers, EndpointS, and other Tools) resource of the FDA-NIH Biomarker Working Group for defining biomarkers [76]. Although we do not have a means to randomize to a treatment control in the current pragmatic design, our stratification in the analysis of veterans based on extent of cognitive control meets the broad definition that a predictive biomarker identifies individuals who are more likely than similar individuals without the biomarker to experience a favorable or unfavorable effect from TMS.

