**Methods:**

Target enrollment consists of 100 veterans with pharmacoresistant Major Depressive Disorder (MDD). All veterans will receive a clinical course of TMS and will be assessed at ‘baseline’ pre-TMS commencement, ‘first week’ after initiation of TMS (targeting five sessions) and ‘post-treatment’ at the completion of TMS (targeting 30 sessions). Veterans will be assessed using functional magnetic resonance imaging (fMRI), a cognitive behavioral performance battery, and established questionnaires. Multivariate linear mixed models will be used to assess whether neural targets change with TMS as a function of dose (Aim 1), whether extent and change of neural target relates to and predicts extent of behavioral performance (Aim 3), and whether extent of neural target change predicts improvement in symptom severity, suicidality, and quality of life (Aim 3). For all three aims, we will also assess the contribution of baseline moderators such as biological sex and age.

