**Discussion:**

To our knowledge, our study will be the first pragmatic, mechanistic observational trial to use fMRI imaging and cognitive-behavioral performance as biomarkers of TMS treatment response in pharmacoresistant MDD. The results of this trial will allow providers to select suitable candidates for TMS treatment and better predict treatment response by assessing circuit connectivity and cognitive-behavioral performance at baseline and during early treatment.

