To evaluate a response biomarker of the effect of TMS on promoting cognitive control. We will assess whether activation and functional connectivity of the DLPFC-anchored cognitive control network, and interactions with sgACC, attention and default mode regions involved, change in a session (akin to dose)-dependent manner. Our broad hypothesis is that functional connectivity will change from the pre-treatment baseline to reassessment early after commencement of TMS (targeting 5 sessions) and later, post- completion of treatment (targeting 30 sessions). Related, we hypothesize that the early change will be most pronounced for patients with intact connectivity at baseline; later change post-treatment will be observed for those with more impaired baseline connectivity. First, we will address the mechanistic question of whether early changes in circuit connectivity are necessary, if not sufficient, for subsequent circuit and clinical changes observed post-TMS. Second, we will systematically test whether the extent of change in connectivity is related to the extent of dysfunction at the pre-stimulation baseline. Third, we will probe whether observed changes in connectivity increase as a session-dependent function of the total number of TMS sessions. In addressing these issues, we will incorporate a methodological technique to quantify the site of DLPFC stimulation with anatomical precision.

### Aim 2

To assess whether the extent of change in a DLPFC cognitive control network connectivity response biomarker is related to corresponding change in behavioral performance. Our broad hypothesis is that the extent of connectivity change will be related to the extent of change in behavioral performance, and that this relationship will be most pronounced for patients with relatively intact connectivity at baseline; later change will be observed in patients with more impaired baseline connectivity.

### Aim 3

To identify if pre-treatment functional connectivity of the DLPFC cognitive control network, involving interactions with the sgACC and regions of the attention and default mode networks, and behavioral performance, along with early change in connectivity and behavior, are predictive biomarkers of clinical outcome. Our hypothesis is that baseline connectivity and behavior, and early and later changes in these measures will predict who at post-treatment have the greatest change in symptom severity, suicidality, and quality of life.

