## Regular care TMS protocol within the partner clinical TMS program of the VA

Veterans will receive TMS treatment as part of their regular clinical care within the VA. Because we will utilize the umbrella VA Clinical TMS Program, we can ensure that the parameters received by veterans are uniform. Treatment will be delivered using the Magstim Rapid 2 or Magstim Horizon Performance devices (The Magstim Company Ltd., Whitland, United Kingdom).

At the time of study design, current clinical practice standards for MDD indicate one session of TMS per day five times per week for 6 weeks. This protocol assumes a magnetic field intensity of 120% of motor threshold at a frequency of 10 Hz at the left DLPFC stimulation site. Treatment sessions take approximately 37.5 min resulting in 3000 pulses per treatment session delivered based on the following treatment parameters: train duration of 4 s, inter-train interval of 26 s, and 75 trains. Stimulation targets are reached through anatomical landmarks using the Beam-F3 method [72].

Depending on veteran treatment response and physician discretion, the standard TMS treatment protocol may be subject to change throughout the treatment course.

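### With every veteran treated and no control group, the design can identify markers of outcome among treated veterans but not markers of benefit from TMS, yet the article says it meets the definition of a predictive biomarker

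*Protocol article*

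**What the plan says.** The Abstract (Methods) states: "All veterans will receive a clinical course of TMS". The Limitations section confirms the design: "Our study is observational and therefore lacks a control group". The next subsection, on the definition of biomarkers, begins "Although we do not have a means to randomize to a treatment control in the current pragmatic design" and then says of the planned stratification by cognitive control that it "meets the broad definition that a predictive biomarker identifies individuals who are more likely than similar individuals without the biomarker". What such people must be more likely to do, in the article's words, is "to experience a favorable or unfavorable effect from TMS". Aim 3 seeks predictive biomarkers of clinical outcome, and the opening of the Discussion repeats the predictive label for the clinical effect of TMS. The Abstract (Discussion) draws the practical conclusion: "The results of this trial will allow providers to select suitable candidates for TMS treatment and better predict treatment response".

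On sessions, Aim 1 treats session number as akin to dose and says "we will probe whether observed changes in connectivity increase as a session-dependent function of the total number of TMS sessions". Assessments are at baseline, after a target of 5 sessions and after a target of 30. The section on the regular care TMS protocol first says that the parameters veterans receive can be kept uniform, and ends: "Depending on veteran treatment response and physician discretion, the standard TMS treatment protocol may be subject to change throughout the treatment course".

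**The concern.** The definition the article adopts is worded as an effect from TMS. An effect is a difference between what happens with treatment and what would have happened without it. For a marker to be predictive in that sense, this difference must vary with the marker. The study observes only the treated side. Improvement among treated veterans also contains natural course, regression to the mean, expectancy and any change in concurrent care, and a marker may be related to any of these.

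The distinction decides what the results can be used for. A prognostic marker says who tends to do well. It does not say who gains from TMS, because a patient with a poor outlook may gain as much as anyone. Choosing candidates for TMS depends on the predictive reading. So does the use mentioned under the longitudinal design, where an early marker might inform discontinuation. These are the study's headline uses.

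Aim 1 raises a related, smaller issue. If session number is read as dose, a time trend or a selective session count could be taken for a dose effect.

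**Working it through.** The point is about identifiability and rests on no figure in the article. The stated 98 veterans (Power calculation) is used below only as a sample size. Whether 98 follows from its own inputs is a separate question.

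**1. What treated-only data can show.** Assume, for illustration, that 40% of marker-positive and 20% of marker-negative veterans respond under TMS. The predictive quantity is

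(treated − untreated response in marker-positive) − (treated − untreated response in marker-negative).

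The untreated rates are not observed. Trying several assumed pairs:

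| Untreated rate, marker+ / marker− | TMS effect, marker+ | TMS effect, marker− | Difference | Reading |
|---|---|---|---|---|
| 40% / 20% | 0.40 − 0.40 = 0.00 | 0.20 − 0.20 = 0.00 | 0.00 | prognostic only; TMS does nothing |
| 30% / 10% | 0.10 | 0.10 | 0.00 | prognostic only; TMS helps both equally |
| 20% / 20% | 0.20 | 0.00 | 0.20 | predictive |
| 10% / 10% | 0.30 | 0.10 | 0.20 | predictive |
| 10% / 20% | 0.30 | 0.00 | 0.30 | predictive |

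The treated data are identical in every row. More patients, more covariates or cross-validation among treated veterans would sharpen the 40% and the 20% but would not choose between the rows.

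**2. How often a purely prognostic marker would look positive.** Assumptions: no TMS effect at all; n = 98; two-sided alpha 0.05; a marker correlated r with natural improvement. The values of r are assumed, since the article gives none. By Fisher's z, the chance of significance is Φ(atanh(r) × √(n − 3) − 1.96), with √95 = 9.747.

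- r = 0.1: 0.1003 × 9.747 = 0.98; Φ(−0.98) ≈ 0.16
- r = 0.2: 0.2027 × 9.747 = 1.98; Φ(0.02) ≈ 0.51
- r = 0.3: 0.3095 × 9.747 = 3.02; Φ(1.06) ≈ 0.85

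**3. Sessions as dose (secondary).** Within a veteran, 0, 5 and 30 sessions occur in the same order as elapsed time and as the first, second and third scan. A trend over sessions is therefore also a trend over time and over repeat testing. Between veterans, 30 sessions is a target rather than an assigned level. If everyone received exactly 30, total sessions would not vary and could not be tested.

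If totals vary and are related to clinical course, the test is biased. A simulation assumed no dose effect, N = 100, clinical course correlated 0.4 with connectivity change, and poorer course leading to more sessions. The two-sided test of total sessions rejected in 5%, 17%, 51% and 82% of runs when session count correlated 0, 0.25, 0.5 and 0.7 with clinical course. Under that assumption the spurious association is negative; the opposite pattern of session changes would make it positive. The article gives none of these correlations.

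**The case against.** The article is open about the design. The missing control group and the definition of biomarkers are the first two limitations it lists, it says plainly that randomising to a control is not possible, and it qualifies the definition as a broad one. It also presents the work as a foundation for later experimental trials. Whether the cited biomarker resource accepts this usage cannot be checked here. All this is fair, but the disclosure is followed by a sentence saying that the definition is met. As the article itself words it, that definition concerns an effect from TMS, and the Abstract and Discussion carry no caveat. The overclaim stands on the article's own words.

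The objection is stronger on dose. A reader might infer that session number is set by response and that the article concludes there is a dose effect. The document supports neither. Dose-dependence is posed throughout as a question. The treatment section says the protocol may change with response and physician discretion, without naming session number. Nor does anything show that all variation in session counts is response-related; missed visits, logistics or tolerability could also cause it. Session is already planned as a repeated measure, and its coding is a detail an article may leave to the full plan. What remains is a limit on interpretation.

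Finally, the 85% should not be read as the probability that the study will mislabel a marker. It is the top of an assumed range and supposes that TMS has no effect.

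**Conclusion.** The statement that stratifying treated veterans meets the definition of a predictive biomarker is wrong as written, and the candidate-selection sentence in the Abstract does not follow from the design. This rests only on two stated facts, that all veterans are treated and that none serve as controls; it depends on no assumed number. The size of the risk cannot be estimated from the document. For assumed correlations of 0.1 to 0.3 and no TMS effect, a purely prognostic marker would be significant about 16% to 85% of the time at n = 98.

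The session-dependence question is legitimate to explore, but the design cannot answer it as a dose question: session number is tied to time and repeat testing, and the total is unassigned and may depend on response. Separately, the statements that treatment parameters are uniform and that the protocol may change during the course sit in the same section and must be reconciled.

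**What to change.** 1. **Limitations, Definition of biomarkers:** delete the claim that stratification meets the predictive definition. Say instead that, without a control group, predictive and prognostic markers cannot be told apart.
2. **Aim 3, opening of the Discussion, and Definition of biomarkers:** describe baseline and early-change markers as prognostic of outcome among TMS-treated veterans.
3. **Abstract, Discussion:** limit the sentence to describing who improves during TMS, and leave candidate selection to a controlled study.
4. **Aim 1:** report change over the treatment course by planned assessment (Baseline, 1 Week, Post-treatment). Present any association with total sessions as descriptive, not as a dose effect.
5. **Regular care TMS protocol:** reconcile the uniformity statement with the statement that the protocol may change.

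None of this needs new patients, data or an added arm. The cost is a less ambitious headline.
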